### Criteria for the addition of milrinone

Milrinone will be commenced in any of the following circumstances to ensure compliance with the Vietnamese MoH guidelines for management of HFMD:Hypertensive emergency, which includes a severe symptomatic elevation in BP (>30 % compared to baseline BP) WITH evidence of acute target organ damage, for example, brain (seizures or increased intracranial pressure), kidneys (renal insufficiency), eyes (papilledema, retinal hemorrhages, or exudates), or heart (heart failure).For children aged 1 year and older:SBP increases to ≥ 99th percentile plus between 5 and 15 mmHg consistently for 30 min.SBP increases to ≥ 99th percentile plus 15 mmHg consistently for 15 minSBP increases to ≥ 40 mmHg over baseline for 15 min and this value is lower than either of the first two cut-offs. The baseline SBP is defined as the lowest value measured at any time after admission to hospital before enrollment in the study.For children aged 6 months to 1 year:SBP increases to ≥ 110 mmHg up to 120 mmHg consistently for 30 min.SBP increases to ≥ 120 mmHg consistently for 15 min.

Occasionally, the clinical status of a patient may indicate that milrinone is not the best inotrope to use. In these cases, the treating physician will make management decisions appropriate to the situation. Similarly, if the patient’s clinical status remains unstable after starting milrinone, additional measures, including ventilation and/or hemofiltration, will be considered in accordance with Vietnamese MoH guidelines for management of HFMD (Additional file 1: Appendix 2). If the BP remains high (SBP > 99th percentile plus > 15 mmHg) despite maximal doses of milrinone and study drug infusion, then additional antihypertensive agents may be added, such as nicardipine, captopril, etc. depending on the clinical scenario.

### Study procedures

#### Screening and recruitment of participants (Fig. 1)

**Fig. 1 Fig1:**
[figure not shown]
Screening flow chart

##### Phase 1 (HTD only)

Initially, recruitment is scheduled to take place at one site (HTD) only to ensure that all study procedures run smoothly during the first few months. Study staff working on PICU at HTD will identify parents or guardians of potentially eligible patients as soon as possible after admission. They consult the hospital chart and the parents/guardians to verify if the initial screening criteria are met, then provide the patient information sheet (PIS, see Additional file 1: Appendix 7) and discuss the study with relevant families. This allows time for the family members to consider the study without pressure to decide immediately. A reference card is completed at this time, defining the specific intra-arterial BP thresholds needed for study enrollment, the addition of milrinone, treatment failure, etc. relevant to that particular individual (by age, sex and length), and this card is attached to the child’s observation chart at the bedside. If the child subsequently develops autonomic disturbance with hypertension exceeding the defined threshold, the study staff go through the PIS a second time with the family and answer any questions before asking for consent, then follow the full pathway for inclusion/exclusion criteria, and if appropriate, proceed to enrollment and randomization (Fig. 1). A case report form (CRF) detailing the history and examination findings at enrollment is completed as soon as the study drug infusion has been started. Children whose parents/guardians do not consent to the study continue with standard care.

Occasionally, patients may present with established Stage 2 hypertension; these individuals have arterial access established immediately, and the process of explaining the study, requesting consent, checking inclusion/exclusion criteria and proceeding to enrolment and randomization, if appropriate, is carried out as quickly as possible, with the aim of commencing the study drug within 30 min. If the BP does not improve within 30 min of commencing the study drug, the milrinone is added. That is, all Stage 2 patients will be on milrinone within 1 h of presentation unless the BP has settled to Stage 1 levels with the study drug.

In case worry over the child’s illness could affect the parents/guardians ability to make an informed decision on study participation, a study doctor goes though the PIS with the family of all participants at least once more in the 12 to 36 h after enrollment or at any time they ask. This review of the PIS is recorded in the CRF.

##### Phase 2 (HTD and CH1)

The study will be established and executed in a similar manner on the HDU at CH1 in due course, with both sites aiming to complete the recruitment over 2 to 3 years.

#### Randomization and blinding

Randomization follows a 1:1 ratio, stratified according to the hospital where recruitment takes place. A randomization list using block randomization with blocks of variable size has been prepared by the Clinical Trial Pharmacist using a computer program and is maintained confidentially from all study staff and treating doctors, including those assessing all trial outcomes. A chronological log of all enrolled patients is maintained by the Pharmacist and the next available sequential study code is assigned to each patient as they enroll. The assigned number corresponds to a coded, sealed, package containing 50 ampoules of 15 % MgSO_4_ or visually matched placebo.

#### Dispensing, storage and accountability

MgSO_4_ 15 % solution and placebo (sterile water) are available in 10 ml visually matched ampoules supplied by Fresenius Kabi. Study drug packages are prepared centrally by the un-blinded Clinical Trials Pharmacist and distributed to the sites as required. Drugs are stored in accordance with the manufacturers’ recommendations in a secure area. All movements of study medication are recorded. Both individual subject and overall drug accountability records are kept up to date. Prior to administration each vial is diluted with 5 ml 0.9 % saline solution by trained study nurses, to give a volume of 15 ml and provide a 10 % MgSO_4_ solution for the magnesium intervention arm.

#### Study drug dose adjustment (Fig. 2)

**Fig. 2 Fig2:**
[figure not shown]
Treatment flow chart

After the initial loading dose, the study infusion dose is increased in 0.1 ml/kg/h stages (10 mg/kg/h) every 15 min to a maximum dose of 0.5 ml/kg/h (50 mg/kg/h), with the following caveats:If the SBP decreases to < 90th percentile for age, sex, and length, the study drug infusion is reduced by one stage every 15 min.If the SBP increases to the levels described below for treatment failure, action is taken as indicated.Plasma Mg levels are measured at least once daily. If the plasma Mg level is > 2.5 mmol/l or < 1.8 mmol/l, an increase or decrease in the infusion rate by 0.1 ml/kg/h is implemented as appropriate. To maintain blinding, plasma Mg values are communicated by the laboratory staff to an independent doctor not involved in the clinical care of the patient, who informs the clinical staff of any dose adjustments to be made to the study drug infusion but does not report the actual laboratory values. Similar (sham) dose adjustments are made for the placebo infusions according to a randomized list available only to the independent doctor. However, the clinicians managing the patient may request unblinding at any time.

#### Discontinuation of the study treatment

If any of the following occur, the study treatment is stopped immediately, and rescue treatment is given as appropriate (Additional file 1: Appendix 5, 6):Serious cardiac arrhythmia (for example, atrio-ventricular block, prolonged QT interval)Hypotension: SBP < 70 + (2 × age) mmHg for 15 min or moreUrine output < 1 ml/kg/h for 4 h or moreCardiac arrest or any other emergency situation where the treating physician feels there is a contra-indication to the study drug.

In addition, if a patient develops respiratory distress (as defined in Additional file 1: Appendix 4), an urgent plasma Mg level will be performed. If intubation and ventilation is needed or if the Mg level is > 3 mmol/l, the study treatment will be stopped, and rescue treatment will be given as described in Additional file 1: Appendix 6.

#### Unblinding

The Clinical Trials Pharmacist holds the unblinded randomization list with details of the contents of each individual treatment package. This list will be accessed only in the case of emergency unblinding, which will be authorized by an investigator following standard operating procedures. Emergency unblinding will be performed in the case of an adverse event when knowledge of the identity of the study treatment may contribute to the treating physician’s ability to care for the patient. In this case, the treating doctor will confirm with the Principal Investigator that unblinding may help inform the care of the patient. If agreed on by the Principal Investigator, the treating doctor may request to know the Mg/Ca lab results or may open the sealed emergency envelopes available on the ward that contain individual patient treatment allocations. In general, in these cases, the study treatment would already have been discontinued as per the “*Discontinuation of study treatment*” paragraph.

#### Clinical assessments and follow-up (Additional file 1: Appendix 8)

All participants remain in the study for the duration of follow-up to 6 months unless the parent/guardian wishes to withdraw, which they may do at any time (see withdrawal section, page 28). In addition to the study procedures outlined below, all patients will receive standard care according to the national treatment guidelines. During the acute phase, patients are examined daily by trained HDU/PICU study doctors. A record of all significant events in the previous 24 h plus detailed physical examination findings (in particular focusing on the nervous system, respiratory, and cardiovascular systems) is recorded each morning in the specially designed CRF. Vital signs are monitored continuously using devices with the facility for download and recording of data into a readable database format using compatible software and/or accessory modules. In a subset of patients, advanced hemodynamic parameters such as CO and SVR are recorded using LiDCO monitoring systems, the subset being determined by the availability of the LiDCO technology at the time when an individual is enrolled and randomized.

A standard ECG recording is performed at the bedside by a trained nurse once daily and also if any abnormality is noted on the monitor by study staff (for example, premature beats, or atrial or ventricular arrhythmias). Urine output is monitored using specific collecting bags and calculated every 4 h. If the urine output is less than 1 ml/kg/h over a 4-h period, a bedside ultrasound scan is done, and if necessary, urethral catheterization is established to monitor the urine output more closely.

Magnesium is an important cofactor in many enzymatic reactions in the body, but the side effect profile is well known, and in the dose range used here, it is generally considered safe (Additional file 1: Appendix 5). However, differentiation between potential magnesium toxicity and progression of HFMD can be difficult. All staff involved in the study have been trained to recognize potential side effects, and a series of standard operating procedures have been put in place indicating when to stop study treatment and/or initiate rescue therapy if any complications occur that might be related to the treatment (Additional file 1: Appendix 6). Similarly, all staff members are aware that they may request an urgent Mg/Ca level at any time or request emergency unblinding in the case of any adverse event when knowledge of the identity of the study treatment might contribute to the treating physician’s ability to care for the patient.

Patients are assessed daily for the duration of the hospital stay. At discharge, full neurological and neurodevelopmental assessments are performed. Patients who have not recovered fully from the effects of sedation with phenobarbitone by the time of discharge, but are otherwise considered fit to go home, are asked to attend 1 week later for formal review and neurological assessment. All patients are also asked to return at 6 months post-enrollment for a clinical and neurodevelopmental assessment. After this, any further follow-up will be according to clinical need, and participants will be referred back to the standard hospital outpatient clinic system.

Neurodevelopmental assessments done at discharge (or 1 week later) and 6 months use the Bayley Scales of Infant Development, Third Edition (Bayley-III) and Movement ABC-2 tools. Children 36 months and under at enrollment will use the Bayley-III. Children 48 months and above at enrollment will use the Movement ABC-2 tool for their assessments.

#### Laboratory assessments and diagnostic testing

The following laboratory tests (see Additional file 1: Appendix 9) are performed on site in the standard hospital laboratories or at the research laboratory of OUCRU in Ho Chi Minh City, except where specifically indicated below:Blood glucose and arterial blood gases are measured at least once daily or more frequently according to the clinical situation.Plasma magnesium and calcium concentrations are measured at baseline and 12 h after the start of the study infusion, then once daily for the remaining 72 h.Plasma electrolytes, creatinine, CKMB and Troponin I are measured at baseline and once daily thereafter.Samples for plasma catecholamine (epinephrine and norepinephrine) concentrations are collected at baseline and then once daily for 72 h, and stored frozen for subsequent analysis in batches. Similarly, a 5-ml aliquot of urine is collected each morning for measurement of urine catecholamines. All urine is collected in appropriate collecting bottles (containing 10 to 15 ml 6 M HCl as preservative) by the bedside and the total volume is recorded at the end of the 24-h period, before the 5-ml aliquot is taken for storage at −20 °C.Samples for plasma cytokine measurements (including IL1, IL6, IL13, and TNF alpha) are collected and stored at −20 °C at baseline and at 12 h and 24 h after starting the MgSO_4_/placebo, with a final sample obtained on discharge from hospital.A nasal/throat swab and a rectal swab are obtained at enrollment, for enterovirus PCR.Serological testing for EV71 and related serotypes within the *Human enterovirus A* species will be done on plasma samples collected at enrolment and discharge. This work will be done in collaboration with laboratories at Duke-NUS in Singapore.With separate consent, cells from participant plasma samples are separated and stored for assessment of host genetic factors associated with disease severity using exome sequencing at The Wellcome Trust Sanger Institute, UK.

#### Adverse Events

Any unfavorable or unexpected sign, including an abnormal laboratory finding, which develops or worsens after commencing the study drug infusion, is documented as an Adverse Event (AE). All clinical AEs are recorded on an AE form, but laboratory abnormalities are only entered on an AE Form if they are accompanied by clinical symptoms, lead to withdrawal of the study drug or modification of the study drug dose, or require a change in concomitant therapy.

Serious Adverse Event (SAEs) are defined as those that result in death, are life threatening at the time, require prolongation of existing hospitalization (>14 days, Additional file 1: Appendix 4), or lead to persistent or significant disability/incapacity.

All SAEs are reported to a) OUCRU as the Sponsor and b) the IRB at the relevant site (HTD or ND1) as soon as possible. A report of any SAE that is life threatening or that results in death is also sent to the office of the Vietnamese MoH Research Ethics Committee. These reports are sent within 7 days of knowledge of the event and include details of the event and the recommendation from the site IRB. If all information is not available upon the initial report, a complete report is sent within 15 days of knowledge of the event. All other SAEs are reported to the MoH Research Ethics Committee, including the recommendation of the site ethical committee, within 15 days of knowledge of the event.

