**Methods/Design:**

We describe the protocol for a randomized, placebo-controlled, double-blind trial of intravenous MgSO_4_ in Vietnamese children diagnosed clinically with HFMD plus ANS dysregulation with systemic hypertension. A loading dose of MgSO_4_ or identical placebo is given over 20 min followed by a maintenance infusion for 72 h according to response, aiming for Mg levels two to three times the normal level in the treatment arm. The primary endpoint is a composite of disease progression within 72 h defined as follows: development of pre-specified blood pressure criteria necessitating the addition of milrinone, the need for ventilation, shock, or death. Secondary endpoints comprise these parameters singly, plus other clinical endpoints including the following: requirement for other inotropic agents; duration of hospitalization; presence of neurological sequelae at discharge in survivors; and neurodevelopmental status assessed 6 months after discharge. The number and severity of adverse events observed in the two treatment arms will also be compared. Based on preliminary data from a case series, and allowing for some losses, 190 patients (95 in each arm) will allow detection of a 50 % reduction in disease progression with 90 % power at a two-sided 5 % significance level.

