### Study endpoints

*The primary endpoint* is a composite endpoint indicating disease progression within 72 h. It is defined as the occurrence of any of the following within 72 h of commencing the study drug infusion:Specific BP criteria necessitating the addition of milrinone as detailed in the section “Criteria for the addition of milrinone” below.Need for mechanical ventilation.Development of shock.Death.

*Secondary endpoints* comprise these parameters singly, plus a number of other clinical endpoints including the following: a requirement for other inotropic agents (for example, dobutamine), duration of hospitalization, presence of neurological sequelae at discharge in survivors, and neurodevelopmental status assessed 6 months after discharge.

*Safety endpoints* include the number of adverse events (AEs) and severe adverse events (SAEs) that occur in the two treatment arms.

*Exploratory endpoints* will be assessed, including serial measurements of cardiac output (CO) and systemic vascular resistance (SVR), catecholamine levels, and cytokine levels. We will assess the impact of MgSO_4_ on these parameters, provided the data collected appear reliable and consistent within individual participants.

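### The definition of a serious adverse event omits readmission and rests on an unclear 14-day cut-off, and the adverse-event counts mix disease progression with possible magnesium toxicity

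*Protocol article*

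**What the plan says.** All references are to the protocol article.

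- **Seriousness (Adverse Events).** "Serious Adverse Event (SAEs) are defined as those that result in death, are life threatening at the time"; the list then continues with events that "require prolongation of existing hospitalization (>14 days, Additional file 1: Appendix 4), or lead to persistent or significant disability/incapacity". No other criterion is given. All SAEs go to the sponsor and the site IRB, and from there, within 7 or 15 days, to the ministry's ethics committee. AEs that are not serious do not take that route.
- **Adverse event (same section).** "Any unfavorable or unexpected sign, including an abnormal laboratory finding, which develops or worsens after commencing the study drug infusion" counts. No exception is made for progression of HFMD. All clinical AEs go on a form, but "laboratory abnormalities are only entered on an AE Form if they are accompanied by clinical symptoms", or if they change the study drug or other therapy.
- **Safety endpoints (Study endpoints).** These "include the number of adverse events (AEs) and severe adverse events (SAEs) that occur in the two treatment arms". The abstract adds: "The number and severity of adverse events observed in the two treatment arms will also be compared". Under Statistical analysis, intensity is graded on five points.
- **Primary endpoint (Study endpoints).** Blood pressure criteria for adding milrinone, ventilation, shock or death within 72 h.
- **Follow-up (Clinical assessments and follow-up).** "All participants remain in the study for the duration of follow-up to 6 months", unless the family withdraws. The same section concedes that "differentiation between potential magnesium toxicity and progression of HFMD can be difficult".

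**The concern.** There are two separate weaknesses.

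The first is classification. The hospitalization criterion covers only the stay in progress, with a 14-day qualifier that can be read in two ways. After discharge, an event can become serious only by being fatal, life-threatening or disabling. Events below that level that bring a child back to hospital, or lengthen the first stay by less than the cut-off, never enter the SAE table or the expedited reports.

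The second is content. Each component of the primary endpoint is also an unfavourable sign that appears or worsens after the infusion starts, so it is also an AE. Death is by definition also an SAE, and shock or ventilation may well be. A count of AEs by arm then carries the efficacy result inside it. If magnesium works as planned, the placebo arm gains AEs through progression, and an excess of toxicity on magnesium may be offset in the total. This matters more here because the protocol itself says that the two are hard to tell apart.

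**Working it through.** **1. Classification under the printed criteria.** The article supports two readings of the 14-day qualifier.

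| Event after the infusion starts | 14 days = total stay | 14 days = extra days |
|---|---|---|
| Fatal, life-threatening or disabling | serious | serious |
| Otherwise, lengthens a stay from 6 to 12 days (invented example) | not serious | not serious |
| Otherwise, carries a stay a few days past day 14 | serious | not serious |
| Otherwise, readmission within 6 months | not serious | not serious |

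The second and fourth rows fall outside on either reading. The third depends on the reading. Under the total-stay reading, slow recovery from HFMD past day 14 could also qualify.

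**2. The plan's own figure.** Inputs from Sample size: 50% v 25%, 90% power, two-sided 5%, 85 per group needed, 95 per arm recruited.

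n = [1.960·√(2·0.375·0.625) + 1.282·√(0.25 + 0.1875)]² / 0.25² = 76.7, that is 77. With the continuity correction this becomes 85, as stated. The design rates can therefore be used as they stand.

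**3. Progression events inside the AE count.** Placebo: 0.50 × 95 = 47.5. Magnesium: 0.25 × 95 = 23.75. Difference: 23.75 children, or 25 percentage points.

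**4. Adding toxicity.** The protocol gives no rate for toxicity-type events, so rates t0 (placebo) and t1 (magnesium) are assumed. Each child has at most one event of each kind, and the two kinds are independent.

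- Events per arm: 95(0.50 + t0) v 95(0.25 + t1). Equal when t1 = t0 + 0.25.
- Children with any AE: 1 − 0.50(1 − t0) v 1 − 0.75(1 − t1). Equal when t1 = 1 − (0.50/0.75)(1 − t0), which is 33%, 37%, 40% and 47% for t0 = 0, 5%, 10% and 20%.
- Power to see toxicity alone at n = 95: Φ{[(t1 − t0)√n − 1.960·√(2t̄(1 − t̄))] / √(t0(1 − t0) + t1(1 − t1))}, where t̄ is the mean of t0 and t1. For 5% v 20%: (1.462 − 0.917)/0.4555 = 1.197, so 88%.

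| Toxicity, placebo v magnesium (assumed) | Events per 95 | Any AE | Power, toxicity alone |
|---|---|---|---|
| 5% v 15% | 52.3 v 38.0 | 52.5% v 36.3% | 63% |
| 5% v 20% | 52.3 v 42.8 | 52.5% v 40.0% | 88% |
| 10% v 20% | 57.0 v 42.8 | 55.0% v 40.0% | 49% |
| 20% v 40% | 66.5 v 61.8 | 60.0% v 55.0% | 86% |

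In every row magnesium has more toxicity, yet the pooled figure favours it. The break-even moves with the assumptions: about 24 children (25 points) if there are no background AEs and toxicity strikes only children who do not progress, and a toxicity rate of 33% to 47% on magnesium if toxicity is independent of progression.

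**The case against.** A reader might infer that the safety endpoint as a whole is insensitive to harm. The documents do not support that. Fatal, life-threatening and disabling events are serious at any length of stay. The 14-day qualifier and the missing readmission criterion affect only the label; a lesser clinical event is still an AE, still graded, and severity is compared by arm. Length of hospital stay is a secondary endpoint with no 14-day floor. The progression components are also analysed singly, so readers will see them by arm. The DSMB receives unblinded tables together with an analysis of clinical outcome, and no section says that it sees a single pooled total.

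The masking in the working needs such a total. The safety endpoints are said to include the counts, which leaves room for more, and the analyses are deferred to a statistical analysis plan that is not shown and may well tabulate by event type. The 14-day wording points to Appendix 4, also not shown, which may settle its meaning.

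There is also a fair objection to the obvious remedy. A table without shock and ventilation could discard toxicity, because magnesium harm may itself appear as hypotension or respiratory distress.

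All of this stands and narrows the point. It does not supply a readmission criterion, and it does not exempt progression from the AE definition: the article fixes both rules in its own text.

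The word *severe* in the safety endpoint is a slip. Adverse Events and the abbreviation list both say *serious*, so it does not show that two different counts are planned.

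**Conclusion.** The point holds in a limited form and should be acted on. The SAE definition is too narrow for a trial with 6 months of follow-up. It leaves out readmission, and its hospitalization criterion cannot be applied uniformly until the 14-day qualifier is explained. What is lost is seriousness status and expedited reporting for events that are neither fatal, life-threatening nor disabling; they are not lost from the AE record. The documents give no figure from which to estimate how many such events there would be.

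The AE and SAE counts also mix efficacy events with possible toxicity. At the design rates, progression alone tilts a pooled count towards magnesium by about 24 children per 95. That figure assumes that the planned effect occurs. Whether it would hide a real harm depends on toxicity rates that the protocol does not give and on how the tables are laid out, so it is a risk to guard against and not a demonstrated failure.

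**What to change.** 1. In Adverse Events, count as serious any AE that leads to readmission during the 6-month follow-up.
2. Replace the bare 14-day cut-off with prolongation of the stay attributable to the AE, and reconcile it with Appendix 4.
3. Report AEs and SAEs overall and again with the primary-endpoint components shown separately. Keep the all-events table as the main one, for the reason given under the objection.
4. Tabulate by arm the events already listed under Discontinuation of the study treatment. They are defined and observed in any case.
5. In Study endpoints, change *severe* to *serious*.

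Items 1 and 2 need a protocol and CRF amendment with ethics approval. The article reports 21 children enrolled by July 2015; their AE forms can be reclassified, and readmission can be asked about at any 6-month visit still to come. The ongoing cost is a few more SAE reports for the sites and one or two extra tables, largely from data already collected. No treatment rule changes.
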